### Patient selection

This study will enroll patients aged 18–80 years who are diagnosed with AIS within 48 h of symptom onset and have a total score ≥10 for both TCM phlegm-dampness and internal-fire syndrome elements, as assessed by the Ischemic Stroke TCM Syndrome Diagnostic Scale (ISDS). The ISDS is a validated instrument developed by our research team (16); the full scale and detailed scoring rules are provided in the Supplementary material. Syndrome differentiation will be performed by at least two attending physicians or higher who have received standardized training on the ISDS. In cases of disagreement, a third senior expert will be consulted to reach a consensus. Inter-rater reliability will be assessed using the Kappa statistic based on 20 pilot cases, with a target Kappa value ≥0.80 indicating good consistency. Regular quality control meetings will be held throughout the trial to ensure consistency in syndrome differentiation.

Patients must also meet the criteria for being at high risk of END, defined as either: (1) MRI showing new ischemic lesions with a DWI-ASPECTS score ≤ 7; or (2) at least two of the following clinically established risk factors for END: hypertension, diabetes mellitus, atrial fibrillation, hyperglycemia at admission, baseline NIHSS score, large vessel occlusion (internal carotid artery or middle cerebral artery M1 segment), or elevated peripheral inflammatory markers. These criteria are based on current evidence and guidelines for END prediction (5, 17–19). The detailed inclusion and exclusion criteria are provided in Table 1.

**Table 1 T1:** Inclusion and exclusion of the QUIET trial.

Inclusion criteria
1. Inpatients diagnosed with AIS.
2. Patients diagnosed with phlegm-heat syndrome based on the Ischemic Stroke TCM Syndrome Diagnostic Scale (ISDS).
3. Patients at high risk of END, defined as either: (1) MRI showing new ischemic lesions with a DWI-ASPECTS score ≤ 7; or (2) at least two of the following clinically established risk factors for END: hypertension, diabetes mellitus, atrial fibrillation, hyperglycemia at admission, baseline NIHSS score, large vessel occlusion (internal carotid artery or middle cerebral artery M1 segment), or elevated peripheral inflammatory markers.
4. Acute ischemic stroke within 48 hours after symptom onset (interval from symptom onset to eligibility screening and enrollment)
5. Aged 18–80 years, male or female.

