### Randomization, allocation, and blinding

Eligible patients will be randomly assigned (1:1) to the intervention or control group using permuted block randomization with a block size of 4, stratified by centre. The allocation sequence, generated and kept under confidential seal by an independent biostatistician using the SAS 9.4 PROCPLAN, will simultaneously serve as the drug-code list for labeling the identical packages of trial medication and matched placebo.

To maintain blinding, QHF and placebo granules are identical in appearance, taste, smell, and weight, and are produced by New Green Pharmaceutical Co., Ltd. All investigators, patients, statisticians, and outcome assessors will remain blinded to group assignment throughout the trial until the blind codes are unlocked. All adverse events will be reported using standardized terminology without revealing group assignment, and concomitant medications with potential unblinding effects (e.g., TCM treatments with similar efficacy) are strictly prohibited. Regular monitoring will assess blinding integrity, with any breaches documented and reported.

Emergency unblinding will be permitted only for serious adverse events (SAEs) where knowledge of treatment assignment is essential for patient management. Requests must be approved by the principal investigator or an independent Data Safety Monitoring Board (DSMB) member and executed via a secure web-based system or sealed envelope. All unblinding events will be documented, and affected participants will be excluded from per-protocol analyses while others remain blinded.

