### Efficacy outcomes

The primary outcome is the proportion of END within 7 days of stroke onset, defined as an NIHSS score increase of ≥2 points compared with baseline. Secondary outcomes are as follows: (1) change in neurological deficit from baseline to 10 days after randomization; (2) the proportion of patients achieving a good functional outcome, defined as a modified Rankin Scale (mRS) score ≤ 2 on day 30 and 90; (3) activities of daily living measured by Barthel Index (BI) on day 30 and 90.

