### Statistical analyses

Statistical analyses will be conducted using three datasets: the full analysis set (FAS), the per-protocol set (PPS), and the safety set (SS). The FAS will include all randomized participants with at least one post-baseline assessment, with missing data imputed using the multiple-imputation method (23). Sensitivity analyses will be conducted using last observation carried forward (LOCF), worst-case, and best-case scenarios to assess the robustness of the primary outcome under different missing data assumptions. The PPS will comprise only those who fully comply with the protocol without major deviations. The SS will include all participants who receive at least one dose of the study drug and undergo at least one safety evaluation. Both efficacy and safety analyses will follow the intention-to-treat principle. Qualitative variables will be summarized using frequencies and percentages, while quantitative variables will be presented as means ± standard deviations for normally distributed data or medians with interquartile ranges for non-normally distributed data.

For the primary efficacy outcome, the incidence of END will be compared between groups using the chi-square or Fisher exact test, as appropriate. Risk differences and 95% confidence intervals will be reported. Secondary efficacy outcomes such as BI scores, changes in NIHSS scores, and relevant biomarkers will also be compared between groups using Student's *t*-test or the Wilcoxon rank-sum test, with mean differences and 95% confidence intervals reported where applicable. Additionally, the proportion of patients with a mRS grade ≤ 2 and the incidence of AEs will be compared using the chi-square test or Fisher exact test, as appropriate.

Prespecified subgroup analyses for the primary outcome will be performed according to the following baseline characteristics: age (>65 years vs. ≤ 65 years); sex (female vs. male); symptom onset to randomization time ( ≤ 24 h vs. >24 h); medical history (hypertension, diabetes mellitus, coronary heart disease, stroke, and hypercholesterolemia); smoking history; Trial of Org 10172 in acute stroke treatment (TOAST) classification; presence of large artery stenosis; stroke severity based on baseline NIHSS score ( ≤ 5 vs. >5); and severity of phlegm-heat syndrome.

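### The primary END comparison is a valid but unadjusted two-by-two test that leaves out baseline NIHSS, a collected variable the protocol itself names as an END risk factor; the cost is modest efficiency and exposure to chance severity imbalance

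*Protocol article*

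**What the plan says.** Under Statistical analyses in the protocol article, the primary outcome is handled thus: "the incidence of END will be compared between groups using the chi-square or Fisher exact test, as appropriate". The effect measure follows: "Risk differences and 95% confidence intervals will be reported". The good-functional-outcome endpoint is treated in the same way: "the proportion of patients with a mRS grade ≤ 2 and the incidence of AEs will be compared using the chi-square test", with Fisher's test as the alternative. The article names no covariate-adjusted or stratified analysis.

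Other sections bear on that choice:

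- **Patient selection and Table 1** count baseline severity among the "clinically established risk factors for END: hypertension, diabetes mellitus, atrial fibrillation, hyperglycemia at admission, baseline NIHSS score", with no cut-off, direction or size.
- **Efficacy outcomes** defines END from the same scale, "defined as an NIHSS score increase of ≥2 points compared with baseline", and Table 2 schedules NIHSS at baseline. The covariate is therefore available wherever the endpoint can be scored.
- **Randomization, allocation, and blinding** specifies "permuted block randomization with a block size of 4, stratified by centre". Severity is not a stratification factor.
- The only analytic use of baseline NIHSS as a covariate is a subgroup split at 5 points. That split does not correct the overall estimate.

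**The concern.** The protocol uses baseline NIHSS as a marker of END risk when it selects patients, then ignores it when it compares the arms. Two things follow if the protocol's own description is right. First, a collected prognostic variable that could narrow the confidence interval is not used. Second, with 36 per arm and no stratification on severity, one arm may by chance be more severe, and the raw risk difference then carries that imbalance into what the trial reports as its preliminary signal.

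This matters despite the pilot label. Study design states a superiority hypothesis on END, and the end of Statistical analyses sets a two-sided test at p < 0.05. The method is stated in the article, so this is a choice made there and not a detail left to an unseen analysis plan.

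**Working it through.** **No figure to reproduce.** Sample size calculation states that no formal calculation was done, so there is no planned power or effect size.

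**Inputs from the protocol:** 36 per arm, 1:1; two-sided 0.05; END 5–40% under usual care (Introduction, as background and not as a design assumption).

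**Assumptions (not in the documents):** arm-specific END rates, and a baseline NIHSS–END odds ratio (OR) of 1, 1.5, 2 or 3 per SD.

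**1. Starting power.** Unadjusted power for a halving of END risk is 8%, 12%, 22%, 33% and 46% at control rates of 5%, 10%, 20%, 30% and 40%.

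**2. Gain from adjustment.** Simulation, 3,000–4,000 trials per scenario, logistic outcome with a standard normal baseline covariate. Likelihood-ratio (LR) tests are compared with each other, so that the conservatism of Fisher's test is not credited to the covariate. Power with baseline NIHSS as the only covariate, unadjusted → adjusted:

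| END, placebo vs QHF | OR 1.5 | OR 2 | OR 3 |
|---|---|---|---|
| 20% vs 10% | 22.8 → 24.2 | 23.9 → 26.1 | 23.2 → 27.6 |
| 30% vs 15% | 35.6 → 36.6 | 35.0 → 37.0 | 34.2 → 39.6 |
| 40% vs 20% | 46.1 → 46.4 | 50.0 → 51.9 | 46.9 → 53.2 |
| 30% vs 10% | 59.0 → 59.6 | 58.6 → 62.1 | 58.1 → 64.3 |

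The Monte Carlo standard error of one power figure is at most √(0.25/3000) = 0.9 points.

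A second simulation with both baseline NIHSS and centre in the model gives gains of about 0–2, 2–3 and 6–7 points at OR 1.5, 2 and 3. The variance of the standardised risk difference changes by about 0 to +2%, −4 to −8% and −11 to −16%. With no association (OR 1) precision is about 3% worse; with NIHSS alone in the model the loss is about 1.5%.

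**3. Type I error.** At 30% vs 30%, chi-square rejects in 4.5–5.7% of simulated trials and the adjusted model with centre in about 5.5%. The planned test keeps its level.

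**4. Chance imbalance.** The SD of the between-arm difference in standardised baseline NIHSS is √(2/36) = 0.236. So P(|d| > 0.25) = 2 × [1 − Φ(0.25/0.236)] = 2 × [1 − Φ(1.06)] = 0.29.

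With no treatment effect, END 30% and the control arm 0.3 SD more severe, the simulated raw risk difference moves by −2.4, −4.2 and −5.8 points at OR 1.5, 2 and 3. The adjusted estimate stays within 0.2 points of zero. Scaled to 0.25 SD (× 0.25/0.3), the shifts are about 2.0, 3.5 and 4.8 points.

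**5. Scale of that shift.** The 95% CI half-width is 1.96 × √[(0.3×0.7 + 0.1×0.9)/36] = 17.9 points for 30% vs 10%, and 1.96 × √[(0.4×0.6 + 0.2×0.8)/36] = 20.7 points for 40% vs 20%. A 3.5-point shift is about a quarter of a 15-point effect (30% to 15%) but well inside either interval.

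**6. Events available to a model.** For a halving of risk: 36 × (0.20 + 0.10) = 10.8; 36 × (0.30 + 0.15) = 16.2; 36 × (0.40 + 0.20) = 21.6. At the bottom of the quoted range: 36 × (0.05 + 0.025) = 2.7.

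**The case against.** The strongest reply is that nothing here is wrong. A chi-square or Fisher test after randomisation is valid, the risk difference is a sensible measure, and ordinary imbalance is already covered by the unadjusted confidence interval. The trial is a pilot with no power target, and a supportive adjusted analysis may sit in the unseen analysis plan. Prognostic strength is also uncertain: entry requires low DWI-ASPECTS or at least two risk factors, so patients with a low NIHSS qualify through other risks, which can weaken the association among those enrolled. With 11–22 events, a model brings its own dependence on assumptions, and switching estimator when events look few would add an analyst's choice to the primary analysis.

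Most of this stands, and it limits the point to efficiency and conditional accuracy. It does not remove it. The question is which analysis is primary, and the article settles that in favour of the one that omits a variable it calls prognostic, while still testing superiority at p < 0.05.

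A reader might infer that the planned test is biased or inflates type I error. The simulations show neither over repeated randomisation. A reader might also infer a large power loss. Gains of 10–12 points appear only at a baseline NIHSS–END correlation of 0.5, which at END 30% is an OR of about 4.5 per SD; the documents give no support for an association that strong.

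**Conclusion.** The point holds as one of efficiency and of sensitivity to chance severity imbalance. The gain is about 0–2, 2–3 or 6–7 power points at an assumed OR of 1.5, 2 or 3 per SD, with a small precision loss if baseline NIHSS turns out not to be prognostic in this enriched population. At END 30%, a 0.25 SD imbalance, which is exceeded with probability 29%, moves the raw estimate by roughly 2–5 points; that is noticeable but small beside the sampling error.

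Adjustment does not rescue the trial's power: for a halving of risk, adjusted power with NIHSS in the model stays at or below about 53% in the scenarios tabulated. Nor does the same argument carry over to mRS ≤ 2 on the documents' own evidence, because they state no link between baseline NIHSS and mRS. Under assumed rates of 50% vs 70%, power would rise from about 41% to 44.7%, 49.3% or 52.6% at OR 2, 3 or 4 per SD, but both the rates and the association are assumptions.

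The change is worth making because it is nearly free. Confidence in its direction rests on the protocol's own risk-factor list; its size rests on assumed values.

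**What to change.** Amend the primary-outcome paragraph under Statistical analyses before unblinding:

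- Make the primary END analysis a logistic model with treatment, baseline NIHSS (continuous) and centre, and report the standardised (marginal) risk difference with its 95% CI. The effect measure already promised is unchanged.
- Keep the chi-square/Fisher comparison as the supportive analysis.
- Fix the estimation method in advance: either Firth-penalised logistic regression throughout, or a stated event-count threshold. This avoids a data-driven switch.
- Optionally, use the same model for mRS ≤ 2 at days 30 and 90, as a secondary extension.

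The cost is one paragraph of text and a short program, with no new data or patients. The downsides are some model dependence with few events and a slight loss of precision if baseline NIHSS is not prognostic here.

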### Recruitment of participants

This study will recruit 72 patients diagnosed with AIS. Open recruitment for AIS patients will be performed both in Dongzhimen Hospital of Beijing University of Chinese Medicine (Beijing, China) and Fangshan Hospital of Beijing University of Chinese Medicine (Beijing, China). Recruitment advertisements will be displayed online and on hospital notice boards, allowing patients to voluntarily contact investigators. Potential patients will be screened for eligibility based on the inclusion and exclusion criteria. Eligible patients will be informed of the risks and benefits of the study. If they agree to participate in the study, patients and/or their representatives will sign the informed consent form. Patient enrollment will begin in December 2025 and end in October 2026. The schematic diagram of the patient timeline is presented in Figure 1.

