Nevertheless, certain limitations should not be ignored. First, this is a single-center pilot trial with a relatively small sample size, limiting statistical power. Second, as an exploratory study, it has not yet completed long-term follow-up or multi-center validation, and thus cannot provide high-level evidence for subsequent large-scale trials.

In summary, the QUIET trial aims to determine whether the early initiation of QHF within 48 h of stroke onset reduces the incidence of END in AIS patients compared with placebo. If the results are positive, this study will provide robust evidence for the prevention and treatment of END in AIS, thereby reshaping and optimizing therapeutic strategies for this condition.

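### Randomisation is stratified by centre but the primary END comparison ignores centre: a small, conservative mismatch that a centre-stratified risk difference removes at no cost

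*Protocol article*

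**What the plan says.** - **Design.** The protocol article (Randomization, allocation, and blinding) assigns patients 1:1 by "permuted block randomization with a block size of 4, stratified by centre". Recruitment of participants names two hospitals ("Open recruitment for AIS patients will be performed both in Dongzhimen Hospital" and a second one) and a total of 72 patients. Sample size calculation gives 36 per group and says that no formal calculation was made.
- **Primary analysis.** Under Statistical analyses, "the incidence of END will be compared between groups using the chi-square or Fisher exact test, as appropriate". Risk differences with 95% confidence intervals are to be reported. No stratified test or centre term is named, and centre is not among the subgroups. The proportion with mRS ≤ 2 is handled by the same pair of tests.
- **Missing data.** The full analysis set is analysed "with missing data imputed using the multiple-imputation method".
- **Number of centres.** The limitations paragraph of the Discussion says "this is a single-center pilot trial with a relatively small sample size". That contradicts the recruitment and randomisation sections, and also Data management and quality assurance, which speaks of study sites in the plural.

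**The concern.** Stratified allocation balances the arms within each hospital, so between-hospital variation in END drops out of the treatment contrast. A chi-square test or simple risk difference that treats the 72 patients as one sample still counts that variation in its standard error. If the hospitals differ in END rate, the standard error is too large, the p-value too high and the interval too wide. With 36 per arm, there is little precision to give away.

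The second strand is that the test and the dataset do not fit together fully. Rubin's rules combine an estimate and its standard error over imputed datasets, and Fisher's test supplies neither.

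The centre count matters to both the report and the analysis: with one centre the stratification point would disappear.

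**Working it through.** **Inputs from the article:** 36 per arm; two centres; allocation balanced within centre; two-sided 5% level; chi-square or Fisher. There is no stated power or END rate to reproduce.

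**Assumptions:** the END rates by centre; the split of each arm over the centres (18/18 or 26/10); exact balance within centre; a switch to Fisher when an expected count is below 5; Wald intervals for coverage. The article's only END range is 5% to 40% (Introduction, background).

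**Step 1: standard error of the risk difference with no treatment effect.** Let p_c be the rate and n_c the number per arm in centre c, w_c = n_c/36, and p̄ = Σ w_c p_c.

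- Unstratified: SE² = 2 p̄(1 − p̄)/36
- True under stratified allocation: SE² = Σ w_c² · 2 p_c(1 − p_c)/n_c
- The excess is 2 Σ w_c (p_c − p̄)²/36, which is zero or positive. Ignoring centre can only overstate the variance.

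For 20%/40% with an 18/18 split:
- unstratified √(2 × 0.30 × 0.70/36) = 0.1080
- true √(0.25 × (0.32 + 0.48)/18) = 0.1054
- ratio 1.025

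For 10%/50% with an 18/18 split:
- unstratified 0.1080
- true √(0.25 × (0.18 + 0.50)/18) = 0.0972
- ratio 1.111

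**Step 2: exact type I error.** All outcomes were enumerated with binomial probabilities. The planned rule is chi-square, or Fisher if an expected count is below 5.

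| END rate, centre 1 / 2 | Split per arm | SE ratio | Chi-square | Planned rule | CMH |
|---|---|---|---|---|---|
| 20% / 20% | 18/18 | 1.000 | 0.0491 | 0.0471 | 0.0498 |
| 30% / 30% | 18/18 | 1.000 | 0.0525 | 0.0525 | 0.0505 |
| 20% / 30% | 18/18 | 1.007 | 0.0476 | 0.0474 | 0.0495 |
| 15% / 25% | 26/10 | 1.007 | 0.0488 | 0.0440 | 0.0501 |
| 20% / 40% | 18/18 | 1.025 | 0.0469 | 0.0469 | 0.0502 |
| 10% / 30% | 26/10 | 1.032 | 0.0453 | 0.0357 | 0.0492 |
| 10% / 50% | 18/18 | 1.111 | 0.0312 | 0.0312 | 0.0494 |
| 10% / 50% | 26/10 | 1.113 | 0.0282 | 0.0276 | 0.0481 |

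The one value clearly above 5% (0.0525) occurs with no centre difference. It reflects discreteness, not stratification. Where the planned rule falls well below chi-square (15%/25% and 10%/30%), the extra loss comes from Fisher's own conservatism.

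**Step 3: exact power if QHF halves the rate in each centre.**

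| Control rate, centre 1 / 2 | Split per arm | Planned rule | CMH | Difference |
|---|---|---|---|---|
| 30% / 30% | 18/18 | 0.326 | 0.330 | 0.004 |
| 20% / 40% | 18/18 | 0.323 | 0.342 | 0.019 |
| 20% / 40% | 26/10 | 0.267 | 0.284 | 0.017 |
| 10% / 50% | 18/18 | 0.314 | 0.376 | 0.062 |
| 10% / 50% | 26/10 | 0.192 | 0.255 | 0.063 |

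**Step 4: coverage of 95% intervals under no effect.** The unstratified Wald interval covers 94.2% to 95.3% for centre gaps up to 20 points and 96.4% to 96.8% at 35 to 40 points. The plain centre-stratified Wald interval covers 93.1% to 93.9% throughout. Stratifying alone therefore does not give a better interval at this size.

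**Step 5: multiple imputation.** Rubin's rules take an estimate and variance from each of m datasets. They report the mean estimate with total variance W + (1 + 1/m)B, where W is the mean within-imputation variance and B the between-imputation variance. A risk difference and its standard error fit this; a Fisher p-value does not.

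**The case against.** The strongest reply is that the harm is small wherever the assumptions are plausible. Both hospitals belong to the same university and apply the same criteria, so an END gap of 30 or 40 points is hard to credit, and a rate of 50% lies outside the article's background range. The trial is described as a feasibility pilot without a power claim. All of this stands, and it is why the point is minor.

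Three stronger readings are tempting, and the documents support none of them.

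- **That the intervals are miscalibrated as planned.** This needs a large centre gap. Up to 20 points, unstratified Wald coverage stays between 94.2% and 95.3%.
- **That the primary analysis cannot be produced on imputed data.** The article also commits to a risk difference with a confidence interval, which Rubin's rules pool directly. Chi-square statistics have a combining rule, and p-values can be combined approximately. The pooling rule and the criterion for switching to Fisher are details that an article may leave to the analysis plan.
- **That Fisher cuts power from 33% to 24%.** That holds only if Fisher is always used. With 36 per arm, an expected count below 5 requires fewer than 10 END events in total. At 30% against 15% this happens in 2.2% of trials, and the planned rule keeps 32.6% power. Fisher is triggered more often at low rates (34% of trials at 20% against 10%), but the loss there comes from the exact test and not from ignoring centre.

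What survives is that the article itself names the primary test, and neither option uses the stratification factor. The pilot label does not remove the point, because the same article states a superiority hypothesis and a 5% significance level.

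**Conclusion.** The point holds as a minor one. The design uses centre, while the primary comparison and its risk difference do not. The consequence is conservative: lost precision, with no inflation of false positives. Under the assumed rates and splits:

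- gaps up to 10 points: standard error inflated by at most 0.8%, which is negligible
- 20 points: standard error inflated by about 2% to 3%, and about 2 points of power or less lost against CMH
- 40 points: type I error about 3%, and about 6 points of power lost

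The documents give neither centre-specific END rates nor expected recruitment by centre, so they do not show which row applies. The Fisher point is narrow: Rubin's rules do not apply directly to that p-value, but the planned effect estimate can be pooled. The contradiction over the number of centres is plain on the page and needs correcting whichever test is used.

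**What to change.** 1. Make the primary analysis the Mantel-Haenszel risk difference stratified by centre, estimated in each imputed dataset and pooled by Rubin's rules.
2. Name a confidence interval suited to small samples, not a plain stratified Wald interval, and say how it is built from the pooled quantities.
3. If a p-value is kept, use the CMH test stratified by centre and state how it is combined over imputations. Fisher's test can remain as a supportive complete-case analysis.
4. Use the same method for the proportion with mRS ≤ 2.
5. Reconcile the single-centre wording in the Discussion with the two hospitals in Recruitment of participants and the centre stratification in the Randomization section.

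The cost is a change of wording and a few lines of analysis code, with no extra patients or data. When the centres do not differ, power is essentially unchanged (0.330 against 0.326 at 30% in both centres).

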### Sample size calculation

Pilot studies are an essential first step to assess the practicality and feasibility of methods and procedures intended for larger-scale investigation (20–22). They should not be used to estimate effect sizes, to provide power calculations for statistical tests or to perform exploratory analyses of efficacy (20). The present work is a pilot randomized controlled trial (RCT) primarily designed to evaluate the feasibility, safety, and preliminary signal of QHF on the incidence of END in AIS patients. No formal sample size calculation was performed; the target of 36 participants per group was considered adequate for exploring the feasibility of study procedures.

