No formal interim analysis is planned for this trial. However, an independent Data Safety Monitoring Board will regularly review safety data throughout the study to ensure participant safety. The DSMB may recommend early termination if unexpected safety concerns arise.

All statistics will be evaluated using two-sided tests, and *p* < 0.05 will be considered statistically significant. Statistical analysis will be performed using SAS version 9.4 (SAS Institute Inc.).

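### Subgroup analyses of END by 13 baseline factors in a 72-patient pilot fall under an unadjusted p<0.05 rule and conflict with the principle for pilot studies that the protocol itself cites

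*Protocol article*

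**What the plan says.** Three statements in the protocol article bear on this point.

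- **Statistical analyses, the subgroup list.** "Prespecified subgroup analyses for the primary outcome will be performed according to the following baseline characteristics". The list has age, sex and onset-to-randomization time, then "medical history (hypertension, diabetes mellitus, coronary heart disease, stroke, and hypercholesterolemia"), then smoking, TOAST class, large artery stenosis, baseline NIHSS and severity of phlegm-heat syndrome.
- **Statistical analyses, closing paragraph.** "All statistics will be evaluated using two-sided tests, and *p* < 0.05 will be considered statistically significant". No analysis is exempted, and nothing in the section describes the subgroup results as descriptive or exploratory.
- **Sample size calculation.** The section cites literature on what pilot studies should not be used for: estimating effect sizes, providing power calculations, "or to perform exploratory analyses of efficacy". It then describes this trial as a pilot for feasibility, safety and a preliminary signal on END, and adds: "No formal sample size calculation was performed; the target of 36 participants per group was considered adequate", with feasibility of procedures as the reason.

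The article names the chi-square or Fisher exact test for the overall END comparison. It names no test for the subgroups.

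**The concern.** A subgroup analysis of the primary efficacy outcome is an exploratory efficacy analysis, and the protocol plans 13 of them after citing a principle against such analyses in pilots. The significance rule makes this more than a difference in tone. A subgroup p-value below 0.05 would count as statistically significant under the written rule, and it would also carry the label of being prespecified.

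The trial is small and no power calculation supports it. Many subgroup looks at one sparse binary outcome can produce a chance result of that kind, and the text gives a later author no reason to hold back from claiming it.

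**Working it through.** The protocol states no error rate, power or event rate for the subgroups, so there is no document figure to reproduce.

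**Inputs from the protocol article**
- 72 patients, allocated 1:1, so 36 per arm (Recruitment of participants; Randomization, allocation, and blinding).
- Factor count: 3 (age, sex, onset time) + 5 (medical history) + 5 (smoking, TOAST, stenosis, NIHSS, syndrome severity) = 13.
- Two-sided 5% level for all statistics (Statistical analyses).
- END in 5-40% of patients under usual care (Introduction, a background figure). No rate is assumed for this trial.

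**Step 1: nominal chance of at least one false positive.** For k independent tests of exactly 5% size, this is 1 − 0.95^k.
- k = 13: 1 − 0.95^13 = 0.487, or 49%. The expected number of false positives is 13 × 0.05 = 0.65.
- k = 9 (medical history counted as one factor): 1 − 0.95^9 = 0.370, or 37%.

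**Step 2: simulation without independence or exact size.** I simulated trials with no treatment effect: 36 per arm, 13 binary factors, 4,000 runs per setting. Both strata of every factor were tested. Chi-square was used when the smallest expected count was at least 5, and Fisher otherwise. The assumptions are factor prevalences of 20-65%, correlation between factors of 0 or 0.2, and TOAST and syndrome severity treated as binary because the article gives no levels for them.

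| END rate, both arms | Expected events in 72 | P(at least one p<0.05), correlation 0 | Correlation 0.2 |
|---|---|---|---|
| 5% | 3.6 | 5.7% | 5.5% |
| 10% | 7.2 | 17.8% | 17.8% |
| 20% | 14.4 | 30.7% | 30.9% |
| 30% | 21.6 | 39.4% | 37.7% |
| 40% | 28.8 | 44.4% | 42.6% |

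The simulation error is at most √(0.25/4000) = 0.8 percentage points (one standard error).

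**Step 3: dependence on a test the article does not name.** Over the same END rates and both correlations, the chance of at least one p<0.05 was:
- Fisher only, within strata: 6-35%.
- Uncorrected chi-square only, within strata: 15-52%.
- Interaction test on the log odds ratio with a 0.5 correction: 2-43%.
- Wald interaction test on the risk difference: 31-61%.

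**Step 4: precision in a half-size subgroup.** Assume 18 per arm and END halved by treatment. The 95% half-width of the risk difference is 1.96 × √[(p1(1−p1) + p2(1−p2))/18]. The half-width for the difference between two such subgroups is √2 times that.

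| Assumed rates | Half-width, one subgroup | Half-width, difference between two |
|---|---|---|
| 10% vs 5% | 17 points | 24 points |
| 20% vs 10% | 23 points | 33 points |
| 30% vs 15% | 27 points | 38 points |
| 40% vs 20% | 29 points | 41 points |

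In every row the interval for one subgroup is wider than the assumed effect (5, 10, 15 and 20 points). The subgroup estimates can describe the data, but they cannot support a claim.

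**The case against.** Several objections are fair.

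- **The cited sentence is not a ban.** It is a general statement about pilot studies taken from the literature, and the text that follows gives this trial the aim of a preliminary signal on END. That stands. An overall END comparison can be read as that signal. Thirteen subgroup splits of the same outcome under a significance rule cannot easily be read that way, so a conflict with the cited principle remains.
- **The conflict is wider than the subgroups.** The superiority hypothesis under Study design and the primary and secondary efficacy tests sit against the same sentence. This is true, and it does not excuse the subgroup list.
- **Test choice, multiplicity handling and exploratory labelling often belong in the SAP, which is not shown.** Their absence from the article is therefore not the finding. The finding rests on what the article does fix: the list and a significance rule covering all statistics. A SAP that made the subgroups descriptive would depart from that rule as published.
- **The Discussion already concedes limited power and calls the study exploratory.** It does. It also says that positive results would be robust evidence, though about the overall result. Neither remark changes the rule in Statistical analyses.

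A reader might also infer that END will be tested inside every stratum, so that roughly 26 tests give a nominal 1 − 0.95^26 = 74%. The article does not say so. It names neither within-stratum nor interaction tests and gives no levels for two factors. Strata of different factors also contain the same patients, so the tests are not independent.

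**Conclusion.** The point holds as a conflict within the protocol article and as a loose inferential rule. Thirteen subgroup analyses of END in 72 patients come under an unadjusted p<0.05 threshold, against the principle cited under Sample size calculation.

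The nominal 49% requires 13 independent tests of exactly 5% size. A reader might take it as about an even chance of a spurious finding in this trial, but the documents do not support that, because the tests reuse the same patients and tests on sparse tables often run below 5%. With the chi-square/Fisher choice named for the primary outcome, the figure is about 31-44% at END rates of 20-40% and 6-18% at 5-10%. Those figures rest on assumed prevalences, correlations and binary factors, and on testing both strata of each factor. Other test choices move the result in both directions.

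A reader might also infer that a chance subgroup result will be used to choose the population of a later trial. No section says so; it is a possible use, not a planned one. The primary analysis is untouched. This is a wording correction that is worth making because it is cheap.

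**What to change.** In Statistical analyses, state that the subgroup analyses are exploratory and descriptive. For each factor, report the risk difference in each stratum and the treatment-by-subgroup interaction estimate, all with 95% confidence intervals and no significance claims. In the closing paragraph of that section, exempt the subgroup analyses from the p<0.05 rule.

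Reconcile this with Sample size calculation, because descriptive subgroup estimates still sit uneasily beside the cited principle. One sentence saying that these results are hypothesis-generating only would do.

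Shortening the list is optional and the sponsor's choice, since all 13 factors can be shown descriptively. A multiplicity correction is not needed once significance claims are dropped.

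The change costs a few sentences and affects neither enrolment nor data collection. The downside is that no subgroup result could be reported as statistically significant.
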